Similarly, Contractor et al. [25] presented a proposal for approaching PTSD that advocates the incorporation of techniques that focus on positive autobiographical memories into trauma-focused treatments. This model was recently updated [26] and was tested in a pilot study [27], and the results showed that the narration of specific positive memories had beneficial impacts on the severity of PTSD symptoms. From this proposal, techniques focused on positive memories would have an effect on the reduction in the severity of PTSD in three ways: (1) direct effects on the severity of PTSD (e.g. through the increase in positive affect and the decrease in negative affect, the development of adaptive cognitions and the increase in the specificity of autobiographical memory), (2) increased effects of trauma-focused interventions (e.g. decreased fear of discussing memories related to trauma and increased preparedness to begin a trauma-focused intervention), and (3) effects on the ease and effectiveness of the processing of traumatic memories (i.e. through an increase in the availability of information and positive experiences that can help to modify the emotional structures related to the trauma, also replacing positive memory to trauma memory as the main point of reference and positively influencing identity and self-concept). Additionally, the incorporation of positive memories has a potential effect in reducing dropout rates (which is important in trauma-focused treatments) and improving treatment adherence and therapeutic alliance.

However, the effect of focusing on positive memories remains to be explored, and it is necessary to continue developing and evaluating intervention proposals focused on the processing of specific positive memories, which are conceived as complementary to trauma-focused interventions. Moreover, this type of proposal is an interesting alternative to solving some of the problems detected in the available interventions for the treatment of trauma in female survivors of IPV.

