### Objectives

The *general objective* of the study is to develop and evaluate the efficacy and effectiveness of an evidence-based psychological intervention program focused on trauma that incorporates positive memories into treatment programs for women who have survived IPV. This general objective is divided into the following *specific objectives*:Design of an empirically validated psychological intervention program for women who have survived IPV and have posttraumatic symptoms that incorporates the approach of positive memories into a cognitive-behavioural treatment program focused on trauma.Application and evaluation of the effectiveness of the program focused on positive memories in women who have survived IPV and have posttraumatic symptoms, considering the following:Posttraumatic symptoms, including general posttraumatic symptoms and PTSD symptomsVariables associated with violence, including experience of violence (physical, sexual and psychological), acceptability of violence; victim blaming attitudes; and motivation for leaving the relationshipMeanings associated with trauma, including thoughts about the self, the world and the future; self-concept and identity; and centrality of traumaPositive and negative affect and regulation of positive and negative affectAssociated symptoms, including anxiety, depression, self-esteem, emotional dysregulation, and general health

To determine the efficacy, the following will be assessed:The effects achieved by the program focused on positive memories compared to a control group on the waiting listThe differential effects of the cognitive-behavioural treatment program with and without the incorporation of the module corresponding to the approach of positive memoriesThe effects achieved by the program focused on positive memories over time (considering follow-up periods of up to 1 year)The clinical significance of the changes obtained by the treatment(3)Evaluation of the implementation and effectiveness of the program, assessed through:Adherence to treatment (estimated by the rates of rejections, dropouts and fulfilment of tasks)The satisfaction of women with treatmentTherapists’ satisfaction with the treatment

The *complementary objective* of the project is the development and, where appropriate, translation and validation of instruments for the evaluation of the different variables considered in the study for which there are no versions and adaptations for the Spanish population.

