### Procedure

Once the participants are recruited through the collaborating centres, the members of the research team contact them, and an appointment is made to carry out the initial screening. Those participants who meet the inclusion criteria are informed of the project and the possibility of participating in it. If they agree to participate, informed consent will be signed, and an appointment will be made with them to carry out the initial evaluation. Those women who do not meet the inclusion criteria or who show their desire not to participate in the project are referred to the centres so that they can receive assistance.

The evaluation is carried out by trained psychologists who are blinded to the treatment modality. Once the initial evaluation is completed, the participants are assigned to a therapeutic group based on their time availability. The determination of the treatment modality of each group is determined randomly using the random number generator of the University of Granada (https://www.ugr.es/~jsalinas/Aleatorios.htm).

The application of the treatment is preceded by an informative-motivational session in which the participants are informed of the characteristics of the program and the presentation of the research team is made.

The treatment is developed in 8 weekly sessions, and thus, it lasts approximately 2 months. In the case of the participants assigned to the waiting list control group, a new evaluation is performed (with the same instruments as in the pretreatment evaluation) after 2 months (i.e. period equivalent to the duration of the treatments), and they are offered the possibility of participating in the treatment in case of acceptance of such participation. The therapists are also psychologists with clinical training who do not participate in the initial evaluation of the participants or in the subsequent evaluations and who are trained in the application of the different treatment modalities. In each treatment group, there are a therapist and a co-therapist in charge of assisting the therapist in carrying out the tasks during the session and in the delivery and collection of materials. The co-therapists are students with training in clinical psychology.

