### Statistical analysis

For the graphic description of the flow of the participants throughout the protocol, the CONSORT diagram is used. The intention-to-treat (ITT) method will also be used. In the treatment of the missing values, it will be checked if the loss of data occurs completely at random using Little’s MCAR test, and then, the estimation of the missing values will follow the maximum likelihood method through the EM algorithm [73].

As a step prior to determining the effectiveness of the intervention programs, the homogeneity of the groups will be analysed, taking into account all the variables evaluated and using *χ*^2^ tests and ANOVAs according to the type of variables.

To determine if the treatment is better than the control group, one-factor (type of intervention) ANOVAs and ANCOVAs will be performed for each of the scores in the posttreatment (or second pre measure for the control group on the waiting list) of the continuous treatment outcome variables, using in the ANCOVAs the value of the pretreatment evaluation as covariance. In the case of ANOVAs, the DSM or Games-Howel tests will be used for post hoc analyses depending on whether the assumption of equality of variances is met. In the case of significant differences in the ANCOVAs, the groups will be analysed in pairs using new ANCOVAs. For those variables that do not adjust to normality, the corresponding nonparametric tests will be applied (i.e. Kruskal–Wallis and Mann–Whitney *U* for pairwise comparisons). For the qualitative variables, *χ*^2^tests will be used.

To determine the changes over time, the two basic moments will be analysed first (i.e. the changes from pretreatment to posttreatment or the second premeasure for the control group). Repeated-measures ANOVAs will be performed in a mixed design with an intergroup factor with three levels (the two treatments plus the control group) and an intrasubject factor (pre and post measures). In those variables that do not adjust to normality, the corresponding nonparametric tests will be applied (i.e. Friedman). Additionally, in this case, for the qualitative variables, *χ*^2^ tests will be used.

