To establish the effectiveness of the intervention program, adherence to treatment will be evaluated considering the percentage of dropouts in each group, the session in which dropouts occur, the number of sessions attended by the women who complete the treatment and the fulfilment of homework. For this, the two treatment groups will be compared in these variables through *χ*^2^ tests or, where appropriate, one-way ANOVA.

Finally, for the analysis of the variables related to therapeutic success, multiple regression (for the prediction of the values of quantitative variables) or logistic regression (for the prediction of therapeutic success vs. failure) will be applied. In addition, to the extent that each variable allows, moderation and mediation analyses will be performed with the PROCESS macro for SPSS using the procedure described by Hayes [74].

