## Discussion

This article described the study protocol of an RCT comparing a trauma-focused CBT for female survivors of IPV with versus without the incorporation of positive memory evocation. Consequently, this study first analyses the effect of adding a positive memory module to a trauma-focused CBT for female survivors of IPV.

The primary aim of the study is to try to correct some of the difficulties detected in the treatment of this type of population, improving adherence to treatment, decreasing dropout rates and achieving significant improvements in both the symptomatology and the well-being of the women treated in comparison with other therapeutic options focused exclusively on trauma. In this way, the therapeutic proposal presented here is framed in the model of complex trauma by Courtois [75], particularly enhancing the recovery of trauma with the development of a more integrated and emotionally modulated autobiographical narrative and a gradual reorientation to the present and future, with the creation of new meanings and purposes, and with the reconstruction of a life that is no longer defined by trauma and its effects. Consequently, the treatments will be compared on a broad range of outcomes in addition to PTSD symptoms, including meanings associated with trauma, affect, associated symptoms, quality of life, attitudes towards violence and revictimization.

The present study will contribute to the advancement in the development of intervention programs increasingly adapted to the characteristics and needs of people with complex interpersonal traumas that involve a change and a vital break in the personal future. In addition, it presents the value of starting from a novel approach in which traditional models and treatments focused on trauma are complemented with interventions focused on positive memories. In this way, the results of this project can become a fundamental point of reference to determine the potential and real scope of this new proposal, which, although it has gained relevance in recent years [39], is still in an initial phase. In short, this study introduces a broader view of trauma and its consequences and searches to enhance women’s recovery.

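### Sessions attended are compared only among completers, a subset the module is meant to change, so this secondary comparison can mask or reverse an attendance difference

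*Protocol article*

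**What the plan says.** The adherence paragraph of the Statistical analysis section states that "adherence to treatment will be evaluated considering the percentage of dropouts in each group, the session in which dropouts occur", followed by "the number of sessions attended by the women who complete the treatment and the fulfilment of homework". It then says that "the two treatment groups will be compared in these variables through" chi-square tests or, where suitable, one-way ANOVA. The article thus fixes the measure, the women it is taken in and the test between arms.

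Three other places bear on how to read this:

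- The Background says that "the incorporation of positive memories has a potential effect in reducing dropout rates", and the Discussion puts "improving adherence to treatment, decreasing dropout rates and achieving significant improvements" within the primary aim of the study.
- The Objectives define the construct more narrowly: "Adherence to treatment (estimated by the rates of rejections, dropouts and fulfilment of tasks"). Sessions attended is not in that list.
- The Statistical analysis section also says "The intention-to-treat (ITT) method will also be used". The sentence is general and is not tied to the adherence measures.

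**The concern.** Whether a woman completes treatment is known only after allocation, and the module is designed to influence it. If the module keeps women who would otherwise have left, the CBT-M+ completers include women with no counterpart among the CBT completers. The two sets are then no longer comparable. If the retained women attend somewhat less regularly than the rest, they lower the completer mean in the arm that did better at keeping them. The same mechanism in the other direction could flatter an arm that loses its less engaged women early.

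Session of dropout has a related limit. It has a value only for women who drop out, so a plain comparison of means would use the complementary subset, also formed after allocation. The article does not say how completers enter that comparison.

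At stake is the reading of one secondary adherence measure. It could be reported as showing no effect of the module on attendance, or an unfavourable one, when attendance over everyone allocated was better.

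**Working it through.** **Inputs from the article.** Eight weekly sessions (Procedure: "The treatment is developed in 8 weekly sessions, and thus, it lasts approximately 2 months"). Expected dropout of 30% and 45 women per group (Sample size). That section's inflation reproduces: 31 / (1 − 0.30) = 44.3, rounded up to 45; 3 × 45 = 135. The article gives no figure for sessions attended and no dropout rate by arm, so the remaining inputs are assumptions.

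**Formula.** With dropout proportion d, mean sessions among completers C and mean sessions among dropouts D, the mean over all allocated women is

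M = (1 − d) × C + d × D.

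The planned comparison uses C alone.

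**Case 1, masking.** Assume dropout of 30% in CBT and 15% in CBT-M+, and C = 7 in both arms. The completer difference is 7 − 7 = 0. Over all allocated women:

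| Sessions attended by dropouts (D) | CBT: 0.70 × 7 + 0.30 × D | CBT-M+: 0.85 × 7 + 0.15 × D | Difference |
|---|---|---|---|
| 2 | 5.50 | 6.25 | +0.75 |
| 3 | 5.80 | 6.40 | +0.60 |
| 4 | 6.10 | 6.55 | +0.45 |

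**Case 2, reversal.** Same dropout rates. Assume that 70% of women would complete under either treatment and attend 7.2 sessions on average, that the 15% who complete only because of the module attend 6, and that dropouts attend 3.

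- Completers, CBT: 7.20.
- Completers, CBT-M+: (0.70 × 7.2 + 0.15 × 6) / 0.85 = 5.94 / 0.85 = 6.99.
- Completer difference: 6.99 − 7.20 = −0.21, against the module.
- All allocated, CBT: 0.70 × 7.2 + 0.30 × 3 = 5.04 + 0.90 = 5.94.
- All allocated, CBT-M+: 0.70 × 7.2 + 0.15 × 6 + 0.15 × 3 = 5.04 + 0.90 + 0.45 = 6.39.
- Difference over all allocated: 6.39 − 5.94 = +0.45, in favour of the module.

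The sign in Case 2 does not hinge on D = 3. With D = 2 the means over all allocated women are 5.64 and 6.24 (+0.60); with D = 4 they are 6.24 and 6.54 (+0.30). The completer difference stays at −0.21 because D does not enter it.

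**Does another planned measure see the effect?** Yes. In both cases the dropout percentage is 30% against 15%, and the plan compares the arms on it.

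**The case against.** The strongest reply is that the completer comparison is one of several adherence measures in the same sentence. A reader might infer that the plan hides any benefit or harm of the module on adherence. The article does not support that. The first measure listed is the dropout percentage in each group, which uses all women. In Case 1 the whole gap is the dropout difference rescaled: (0.30 − 0.15) × (7 − D). Women who drop out also enter through the session at which they leave. Dropout rate, timing of dropout and completers' attendance, read together, describe attendance fairly well; what is missing is one unconditional summary. This stands, and it limits the point.

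A reader might also infer that attendance over all women would be the more powerful test. Nothing in the documents shows this. In a simulation with assumed attendance (45 per arm, two-sided 0.05, completers attending 6, 7 or 8 sessions with probabilities 0.1, 0.3 and 0.6, dropouts attending 2, dropout 30% versus 15%), power was 0.42 for the chi-square test on dropout and 0.38 for a t-test on sessions over all women. The reason for the change is validity of the comparison, not power.

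Nor is a fault in the homework analysis established, since the wording does not clearly confine homework to completers.

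Finally, the Objectives do not name sessions attended as a component of adherence, so the stated adherence objective does not rest on this comparison. That also stands.

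The general intention-to-treat sentence does not answer the point. The adherence paragraph names its own, narrower population for sessions attended, and a general statement elsewhere does not undo that.

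**Conclusion.** The point holds in limited form. The planned comparison of sessions attended conditions on completion, which the article expects the module to change, so it cannot be read as a randomised comparison. Under the assumed inputs it shows a difference of 0 where attendance over all allocated women differs by 0.45 to 0.75 sessions, or −0.21 where the difference over all allocated women is +0.45. The size depends on assumed dropout in CBT-M+, attendance of completers and dropouts, and attendance of the women whom the module retains; the documents give none of these. If the module leaves the make-up of the completers unchanged, including equal dropout, this bias does not arise.

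Severity is minor. The measure is secondary, the dropout comparison covers effects that act through dropout, and the primary PTSD outcome is not touched.

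**What to change.** In the adherence paragraph of the Statistical analysis section:

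1. Compare the number of sessions attended, from 0 to 8, over all women allocated to CBT or CBT-M+, counting sessions after dropout as not attended.
2. Analyse session of dropout as time-to-event over the same women, with completers censored at session 8.
3. Keep the attendance of completers as a descriptive figure, without a test between arms.

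The dropout percentage comparison and the homework measure can stay as they are.

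The cost is analysis wording. The Measures section has women complete the weekly anxiety and depression scales and a session satisfaction questionnaire at the end of each of the 8 sessions, so attendance should be derivable for dropouts as well. The article does not state in so many words that an attendance record is kept for them; the sponsor should confirm it.

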## Discussion

This article described the study protocol of an RCT comparing a trauma-focused CBT for female survivors of IPV with versus without the incorporation of positive memory evocation. Consequently, this study first analyses the effect of adding a positive memory module to a trauma-focused CBT for female survivors of IPV.

The primary aim of the study is to try to correct some of the difficulties detected in the treatment of this type of population, improving adherence to treatment, decreasing dropout rates and achieving significant improvements in both the symptomatology and the well-being of the women treated in comparison with other therapeutic options focused exclusively on trauma. In this way, the therapeutic proposal presented here is framed in the model of complex trauma by Courtois [75], particularly enhancing the recovery of trauma with the development of a more integrated and emotionally modulated autobiographical narrative and a gradual reorientation to the present and future, with the creation of new meanings and purposes, and with the reconstruction of a life that is no longer defined by trauma and its effects. Consequently, the treatments will be compared on a broad range of outcomes in addition to PTSD symptoms, including meanings associated with trauma, affect, associated symptoms, quality of life, attitudes towards violence and revictimization.

The present study will contribute to the advancement in the development of intervention programs increasingly adapted to the characteristics and needs of people with complex interpersonal traumas that involve a change and a vital break in the personal future. In addition, it presents the value of starting from a novel approach in which traditional models and treatments focused on trauma are complemented with interventions focused on positive memories. In this way, the results of this project can become a fundamental point of reference to determine the potential and real scope of this new proposal, which, although it has gained relevance in recent years [39], is still in an initial phase. In short, this study introduces a broader view of trauma and its consequences and searches to enhance women’s recovery.

In the design and implementation of the study, the guidelines outlined in the CONSORT statement (http://www.consort-statement.org), as well as the specific guidelines for trauma-focused interventions proposed by the International Society of Traumatic Stress Studies—ISTSS [38] were followed. In addition, this study has several strengths. First, there was a pilot study prior to the clinical trial. In relation to the experience of the pilot study, several modifications were introduced in the study protocol that are key to its evolution, including the introduction of reminder calls of the session to each participant of the group the day before the session, the introduction of a space for informal exchange between the participants of each group at the end of each session, the introduction of a motivational-informative talk at the beginning of the program, the modification of exercises and instructions for some of the contents included in the treatment manual and the incorporation of the co-therapist to assist the therapist in the management and streamlining of group tasks.

Second, the application and evaluation of the positive memory module as a step prior to its incorporation into the CBT [41] is also a strength. This study allowed us to establish the effect of the module while providing information on the guidelines to be followed in its application.

Third, the trial not only focuses on changes in PTSD but also focuses on other symptoms that are common and significant among survivors of IPV (e.g. depression, anxiety, self-concept, emotional dysregulation). In this sense, it is worth mentioning the inclusion of measures to establish the effect of the program on attitudes towards IPV and, above all, on the probability of revictimization, as well as the possible mediating effect of these variables in the reduction of posttraumatic symptomatology, which is especially relevant for the recovery of these women. In addition, the incorporation of this large number of variables, especially those related to the processes, will allow for the establishment of the effect achieved by the treatment as well as the underlying mechanisms and predictors of treatment outcome, which, conversely, will provide insight into how the treatment works and for whom.

Fourth, the study incorporates various instruments to control and evaluate that the applied techniques achieve the desired effect. Thus, in the application of the modules of positive memories and neutral images, the assessment of the emotional state caused by the evocation (i.e. degree of discomfort and degree of well-being) is incorporated, as well as the level of activation that it arouses. This evaluation allows us to verify whether the evocation of neutral images is truly neutral (i.e. low discomfort, low well-being and medium activation) and whether the evocation of positive memories is truly positive (e.g. low discomfort, high well-being and medium or high activation).

A final strength of the study is its application in community settings, which allows, on the one hand, an increase in the ecological validity and representativeness of the results with respect to the usual work with survivors of IPV and, on the other hand, the promotion of the dissemination of the program among professionals who work in direct care of this population, which is one of the basic motivations of this project.

The main difficulty of the study will be the adherence of the participants to the intervention programs. In fact, this is one of the problems that is at the base of the approach of this study and one of the fundamental reasons for the development of the intervention program proposed here. Although the proposed program tries to obviate this problem, adapting as much as possible to the specific circumstances of women, it cannot be forgotten that in most cases, the victims of violence who request assistance (whether legal or psychological) are frequently immersed in a period of vital changes, which can make it difficult for them to attend the sessions and perform the various tasks at home that may be entrusted to them.

Regarding the possible difficulties inherent to the characteristics and application of the program itself, the possible use of positive memories as an avoidance strategy is proposed, as mentioned above. On the other hand, the selection of positive memories not related to the trauma can sometimes be problematic in women who have been immersed in a violent relationship for many years and for whom many of the most positive experiences of their life (e.g. the birth of a son or his wedding day) are related in one way or another to the aggressor.

Regarding the limitations, it should be noted that, as it is proposed, this program is accessible only to women without functional illiteracy in Spanish and with a certain sociocultural level, which limits to some extent its possibilities of application (e.g. immigrant women with little command of Spanish, who, according to the data, are a population at high risk). It would be convenient, therefore, once the effectiveness of the program is established, to make adaptations that allow its application in this type of women.

